**4.3. OUTCOME MEASURES: VALIDITY AND RELIABILITY INDICATORS**

**4.3.1. VALIDITY**
Main indicators for evaluating convergent and discriminant validity of electrophysiological or radiological parameters relative to clinical parameters will be Pearson correlation coefficients (or standardized regression coefficients). According to the pathophysiological hypotheses in section 2.2, we expect:

- Significant positive correlation between the SP/AP ratio in EcoG and severity of each cardinal symptom measured on the corresponding VAS.
- Higher correlation between the pathological-side SP/AP ratio and each cardinal symptom than between SCD anatomical size and surface, proportion of 1 kHz absorbance peaks in WBT, or PEMV alteration and symptom severity measured on the corresponding VAS.
- No correlation between cardinal symptom severity and electrophysiological (or radiological) indicators on the healthy side.
- Moderate correlation between anatomical SCD measurements on CT and PEMV alteration or WBT 1 kHz absorbance peak presence.

Correlation coefficients will also be calculated between combined electrophysiological criteria (EcoG +/- WBT +/- PEMV) and each cardinal symptom severity, between electrophysiological criteria and generic quality of life (EQ-5D-5L), and between electrophysiological criteria and symptom severity on the French Naert questionnaire.

Patient profiles with unilateral SCD will be determined using principal component analysis, supplemented by supervised modeling.

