**Role of electro-physiological findings in the assessment of symptoms severity in Minor syndrom**

University Hospital Toulouse is the sponsor of this research.

This research will be conducted with the support of *nom de la firme pharmaceutique / source of grants (PHRC,…).*

- **Brief summary :** this research aims at assessing the validity of three different electro-physiological tests (Vestibular Evoked Myogenic Potentials, WideBand Tympanometry, Electrocochleography) used in the investigation of the symptoms severity in the case of superior semi-circular canal dehiscence syndrom*.*
- **Detailed description :** Superior semi-circular canal dehiscence (SCD) syndrom can associate several characteristic auditory and vestibular symptoms**.** Recent systematic reviews identified pulsatile tinnitus, autophony, sound-induced and pressure-induced vertigo as most specific signs of SCD. These signs are rarely all present and the symptomatology remains highly variable from a patient to another. A surgical treatment may be proposed when the symptoms are significantly incapacitating. Unfortunately to date, there is no objective marker of this severity and all surgical decisions rely on the importance of patients’ complaints. High Resolution Computed Tomography (HRCT) of the temporal bone can confirm the diagnosis. Electro-physiological investigations such as Vestibular Evoked Myogenic potentials (VEMPs) have also been extensively described in the diagnosis of SCD but they have been reported as independant from the symptoms severity. Wideband tympanometry (WBT) and Electrocochleography (EcoG) have only been studied in few reports but the latter appears as a promising tool in the assessment of the symptoms because it explores inner ear biomechanics, directly involved in the pathophysiology of this condition.

These three electrophysiological tests are non invasive, commonly used in a routine neurotology practise, and provide objective findings that may be studied in relation to the subjective symptoms reported by the patients, on a visual analogue scale and on a questionnaire translated in French from Naert et al. (2021).

Three visits will be planned within one month +/-7 days period. Each visit will take place 15 days after the previous one and will include questionnaires on SCD symptoms severity (visual analogue scale and questionaire from Naert), the three electro-physiological tests (VEMPs, WBT, EcoG) repeated twice.

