**2.4. EXPECTED OUTCOMES**
This study has several novel aspects:

- Inclusion of rarely studied pauci- or asymptomatic patients
- First study combining three electrophysiological tests typically performed separately
- Potential new insights on test reliability through repeated measures

Patient benefits include:

- Identification of objective markers for symptom impact, enhancing pathophysiological understanding
- Potential future use of these markers to guide therapy
- French validation of Naert et al.’s (2021) questionnaire as a patient-perceived quality-of-care tool

Strategically, this will be the first national multicenter study on SCD, increasing visibility for French otology teams in a field largely dominated by North American research.

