**4.1.1.1. PULSATILE TINNITUS**
The presence and severity of unilateral pulsatile tinnitus on the SCD side will be assessed using a visual analog scale (VAS) ranging from 0 (no pulsatile tinnitus) to 100 (extremely disabling pulsatile tinnitus) at each of the three planned visits.

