**5. STUDY DESIGN**

**5.1. JUSTIFICATION OF METHODOLOGICAL CHOICES**
In this study, the objective is to evaluate the validity and reliability of various electrophysiological parameters to better and objectively identify the severity of symptom impact in SCD.

The reliability of a measurement sets the upper limit of the maximum validity it can achieve (Streiner, 2015). The methodological choices made to address the objectives are as follows:

- Selection of patients with unilateral SCD formally diagnosed by temporal bone CT: patients with bilateral SCD will not be included to avoid uncertainty in attributing symptoms to one, the other, or both SCDs.
- No requirement for symptom severity, to obtain a population sufficiently heterogeneous in terms of symptom impact and representative of patients followed in ENT hospital services.
- Stable SCD in a diagnostic and follow-up context, with no therapeutic intervention planned within 3 months of the first visit. This allows evaluation of the test-retest reliability of different electrophysiological parameters, with measurements repeated over 3 successive visits (less than one month apart) and 2 repeated measurements at each visit. These repeated measures will allow assessment of intra-patient reliability (6 repeated measurements), intra-visit reliability (2 repeated measurements per visit), and inter-visit reliability (3 repeated visits).

The evaluation of the validity of electrophysiological measurements will primarily rely on a convergent and divergent validation approach by estimating the associations between each electrophysiological parameter and patient-reported symptoms (cardinal symptoms, Naert questionnaire, and quality of life). The main hypothesis (based on the theoretical model from the literature) is that the SP/AP ratio measured in electrocochleography will be the parameter most strongly correlated with the cardinal symptoms, compared to other electrophysiological parameters. More generally, all correlations obtained in this study between clinical and paraclinical measures will provide a better understanding of the construct validity of the various electrophysiological parameters.

The Naert questionnaire is not yet validated in French. A translation of the scale is underway, and the psychometric properties of this new translated version will be evaluated during this study. Repeated administration of the questionnaire over the 3 follow-up visits will allow assessment of test-retest reliability.

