**6. ELIGIBILITY CRITERIA**

**6.1. INCLUSION CRITERIA**

- Unilateral SCD formally diagnosed by high-resolution CT (≤0.5 mm slices, reconstructions in the plane of the superior semicircular canal and perpendicular plane) of the temporal bone, with no requirement for symptom severity.
- If present, SCD-related symptoms must be stable in a diagnostic and follow-up context, with no therapeutic intervention planned within 3 months of the first visit.
- Adult patient (≥18 years), able to read and understand French.
- Affiliated with or beneficiary of a social security scheme.
- Free, informed, written consent signed by the participant and investigator (at the latest on the day of inclusion and before any study-related examination).

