**11.2. STATISTICAL METHODS**
Data will be described overall; outliers will be identified and corrected if possible. Missing data will be described for the population.

Inclusion/exclusion criteria, patient follow-up, and reasons for early withdrawal will be described, with a flow chart for inclusions and withdrawals.

Reliability of repeated measures will be evaluated first, as it allows further validity assessment:

- Electrophysiological indicators: intra-patient reproducibility (6 repeated measures), inter-visit (3 visits), intra-visit (2 measures per visit) using Bland-Altman plots (1999) with mean bias, 95% CI, and limits of agreement. Adaptation for more than 2 repeated measures will be used for inter-visit or intra-patient reliability (Jones et al., 2011). Intraclass correlation coefficients with 95% CI will also be calculated.
- The same reliability assessment applies to 3 repeated cardinal symptom measures.

If clinical and paraclinical measures are reliable, the validity of indicators will be analyzed using the mean of 6 repeated electrophysiological measures and the mean of 3 repeated clinical symptom measures.

- Convergent validity: correlations between electrophysiological indicators on the pathological (SCD) side and symptoms (presence, intensity, Naert questionnaire)
- Divergent validity: same analyses for the healthy side
- Correlations between electrophysiological indicators, anatomical-radiological measures, symptoms, and quality of life will be described to better understand construct validity.

If inter-visit reliability does not allow use of repeated-measure means, correlations may be estimated using mixed-effect models after standardization of variables. Psychometric properties of the French-translated Naert questionnaire will be assessed (inter-item correlations, item-total correlations, Cronbach’s alpha). Factor analysis will be performed.

Test-retest reproducibility of the Naert questionnaire will be evaluated by intraclass correlation coefficient and Bland-Altman indicators (3 repeated measures across 3 visits).

Unsupervised multivariate descriptive analysis (PCA, clustering) will define patient profiles based on electrophysiological, anatomical, and symptom characteristics. Supervised modeling (partial least squares regression) may also be applied to predict symptoms from multivariable indicators (+/- anatomical indicators).

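### The primary correlation of SP/AP with each symptom VAS mixes presence of the symptom with its severity, so a significant positive r alone cannot show that SP/AP grades severity among affected patients

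*Protocol*

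**What the plan says.** **Measure.** Each cardinal symptom has one VAS (protocol 4.1.1.1 to 4.1.1.4). The tinnitus scale is described as "ranging from 0 (no pulsatile tinnitus) to 100 (extremely disabling pulsatile tinnitus"), and the other three are built the same way. One number thus carries both presence and severity.

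**Population.** Entry rests on CT, "with no requirement for symptom severity" (6.1). Section 5.1 gives the reason: "No requirement for symptom severity, to obtain a population sufficiently heterogeneous in terms of symptom impact". Section 2.4 lists as a novelty the "Inclusion of rarely studied pauci- or asymptomatic patients". The English abstract adds: "These signs are rarely all present and the symptomatology remains highly variable from a patient to another". Zeros are therefore to be expected on each VAS, including among patients who have other symptoms.

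**Analysis.** The main validity indicators "will be Pearson correlation coefficients (or standardized regression coefficients") (4.3.1), and the first expectation is a "Significant positive correlation between the SP/AP ratio in EcoG and severity of each cardinal symptom measured on the corresponding VAS". Section 11.2 uses the mean of the six SP/AP measurements and the mean of the three VAS scores, and lists "correlations between electrophysiological indicators on the pathological (SCD) side and symptoms (presence, intensity, Naert questionnaire"). Neither section restricts the intensity correlation to patients with the symptom.

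**Precision.** Section 11.1 states, for 100 patients, a 95% CI width below 0.30 for a Pearson correlation of 0.50 or more and below 0.40 for a correlation of 0.

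**The concern.** Section 2.1.1 says that management depends on how severe the symptoms are and that no objective tool measures this. Section 2.2 proposes SP/AP elevation as that marker, with possible use in treatment decisions. For that use, SP/AP should distinguish mildly from severely affected patients.

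A correlation over a cohort that includes patients scored 0 does not test this by itself. If SP/AP were merely higher in patients who have the symptom, and unrelated to intensity among them, the whole-cohort correlation would still be positive and could be significant. Listing presence as a further variable in 11.2 does not settle the matter: a marker of presence only would tend to correlate with both presence and intensity, and the two results together would look like confirmation.

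At stake is the wording of the main conclusion. An association with presence or overall impact could be reported as evidence that SP/AP grades severity.

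**Working it through.** **1. The plan's own precision.** Fisher z interval: tanh(atanh(r) ± 1.96/√(n − 3)).

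| n | 95% CI width at r = 0.50 | 95% CI width at r = 0 |
|---|---|---|
| 100 | 0.297 (0.337 to 0.634) | 0.393 (−0.196 to 0.196) |
| 80 | 0.334 | 0.439 |
| 70 | 0.357 | 0.470 |
| 50 | 0.426 | 0.557 |
| 30 | 0.559 | 0.721 |

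The figures in 11.1 reproduce at n = 100 and already fail at n = 80. They fit only a correlation that uses all, or nearly all, patients.

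**2. Model of a presence-only marker.** Let p be the proportion with the symptom. VAS is 0 without it, and has mean m and SD s with it. SP/AP has SD 1 within each group, is shifted by d in patients with the symptom, and is unrelated to VAS among them. Then

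r = p(1 − p)·d·m / √{[1 + p(1 − p)d²]·[p·s² + p(1 − p)m²]}.

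Example with p = 0.5, d = 0.8, m = 50, s = 20: the numerator is 0.25 × 0.8 × 50 = 10. The two brackets are 1 + 0.25 × 0.64 = 1.16 and 0.5 × 400 + 0.25 × 2500 = 825. So r = 10/√(1.16 × 825) = 10/30.9 = 0.32, although the true gradient among affected patients is zero. With n = 100, two-sided p < 0.05 needs r above about 0.197.

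**3. Chance of a significant positive r** (n = 100, r > 0 and two-sided p < 0.05, 20,000 simulated trials per cell). The protocol gives neither the share at 0, nor the shift, nor the VAS distribution; all three are assumptions. Two VAS shapes among patients with the symptom are shown: normal, mean 50 and SD 20; and right-skewed, exponential with mean 25. Both are clipped to 1-100.

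| Share at 0 | Shift d (SD) | Normal VAS: mean r, chance | Skewed VAS: mean r, chance |
|---|---|---|---|
| 30% | 0.5 | 0.18, 44% | 0.11, 20% |
| 50% | 0.5 | 0.21, 57% | 0.15, 31% |
| 70% | 0.5 | 0.20, 53% | 0.15, 32% |
| 30% | 0.8 | 0.28, 82% | 0.17, 41% |
| 50% | 0.8 | 0.32, 93% | 0.23, 63% |
| 70% | 0.8 | 0.31, 90% | 0.23, 65% |

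At d = 0.3 the chance is 19-25% (normal) or 10-15% (skewed). At d = 1.0 it is 94-99% or 57-83%.

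**4. The same trials, patients with the symptom only.** The chance of a significant positive r is 2-3% in every cell, the nominal 2.5%. Restricting to these patients removes the artefact, at the precision shown in step 1 for 70, 50 or 30 patients.

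**The case against.** The strongest reply is that the protocol means to include the zeros. Section 2.1.1 describes asymptomatic to severely impaired patients as one continuum of severity and names the unexplained asymptomatic patients as part of the scientific gap. Section 5.1 drops any severity requirement to obtain that spread. On this view 0 is the low end of severity and the whole-cohort correlation answers the objective in 3.1. This stands: a reader might infer that the whole-cohort correlation is the wrong primary measure, and the documents do not support that.

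A reader might also infer that a presence-only marker would be declared a marker of severity. That goes too far. The protocol sets no formal decision rule: 4.3.1 states expectations, and 11.1 plans for precision rather than for a test. Section 2.2 hypothesises a strong association, and 4.3.1 adds further expectations, including a stronger correlation than for the other tests and none on the healthy side. A presence-only marker with a shift of 0.5-0.8 SD gives a mean r of 0.11-0.32, hardly strong; an observed r of 0.50 or more occurs in under 2% of the trials simulated at those shifts.

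Third, the rate depends on the VAS shape, and skewed scores, plausible when mildly affected patients are enrolled, lower it considerably. This also stands and is why a range is given.

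Last, 11.2 does not say which patients enter the intensity correlation, and an analysis plan not shown here might. But the indicator, its expected result and its n = 100 precision are fixed in the protocol, and they fit the whole cohort. What the main correlation can support should be settled there.

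**Conclusion.** The point holds in a limited form. Because the VAS scores an absent symptom as 0, patients without symptoms are enrolled by design, and the correlation is planned on about 100 patients, the expected significant positive r can come from presence alone. For 30-70% of patients at 0, the chance is about 20-57% at a shift of 0.5 SD and about 40-93% at 0.8 SD, with a mean r of about 0.1-0.3. These figures rest on an assumed share at 0, shift and VAS shape, and on no gradient at all among affected patients. They show what the planned analysis cannot exclude, not what is likely to happen.

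The correlation remains valid as a measure of association with overall symptom impact. What it cannot support alone is the statement that SP/AP grades severity among patients who have the symptom. This should be corrected, since it affects the main conclusion and the data needed are already planned.

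**What to change.** Keep the whole-cohort correlation as the primary measure. In 4.3.1 and 11.2 add, for each cardinal symptom and with 95% CIs:

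- (a) SP/AP against presence of the symptom, in all patients;
- (b) SP/AP against mean VAS, among patients with the symptom, with the definition of having the symptom over the three visits fixed in advance.

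State that a whole-cohort correlation without a gradient in (b) will be reported as an association with presence or overall impact, not as evidence that SP/AP grades severity among affected patients.

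**Cost.** No new data or visits. The price is precision in (b): the 95% CI width at r = 0.50 is about 0.36 / 0.43 / 0.56 with 70 / 50 / 30 symptomatic patients, against 0.30 with 100. With few symptomatic patients, (b) may be too imprecise to show or exclude a gradient, and the report should then say so. These widths belong beside the present figures in 11.1. Making (b) the primary criterion would be a larger change: keeping about 100 patients with a given symptom would need about 143 / 200 / 334 enrolled at an assumed 70 / 50 / 30% with it (100 divided by the proportion). That is not proposed here.

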**2.1.2.2 Wideband Tympanometry (WBT)**
WBT non-invasively measures middle and inner ear mechano-acoustic impedance using a probe delivering a 226–8000 Hz stimulus and measuring reflected energy to calculate absorbance. SCD reduces inner ear impedance, detectable as an absorbance peak at 1 kHz, provided middle ear function is normal. Nakajima et al. (2012) and Merchant et al. (2015) reported WBT sensitivity of 80–93% for SCD diagnosis. No study has yet correlated the 1 kHz absorbance peak with symptom severity.

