**4. OUTCOME MEASURES**

This study aims to evaluate the validity of objective para-clinical assessments (electrophysiological and radiological) in measuring the symptom impact of SCD. This objective is based on the correlation of clinical indicators of symptom severity with para-clinical indicators in a construct validation approach according to the hypotheses described in section 2.2, with:

- convergent validity, by verifying positive correlations between symptom impact and electrophysiological or radiological measurements on the pathological side,
- discriminant validity (or divergent validity), by verifying the absence of correlation between symptom impact and electrophysiological or radiological measurements on the healthy side.

All clinical and para-clinical measurements are detailed below, before presenting the validity and reliability outcome criteria for:

- the validity of EcoG and other objective para-clinical assessments (temporal bone CT, PEMV, WBT),
- the reliability of electrophysiological assessments (EcoG, PEMV, WBT),
- the psychometric properties of the Naert questionnaire translated into French.

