**4.2.1.2. WIDEBAND TYMPANOMETRY (WBT)**
Two WBT recordings are performed at each of the three visits in response to wideband auditory stimulation (226–8000 Hz). They allow determination of the absorbance peak for each of the 6 measurements (see Figure 4), with the frequency of the peak recorded. The proportion of absorbance peaks at 1 kHz (associated with SCD in the literature) across the 6 measurements is also recorded.

*Figure 4: Procedure and typical 1 kHz absorbance peak in SCD (from Eberhard, 2021)*

All recordings are performed by the same examiner within one center using the Titan® tympanometry system (Interacoustics®).

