**4.2.1.3. PEMV**
Two ocular and cervical PEMV recordings are performed at each of the three visits, collecting the PEMV threshold (dB SPL) and wave amplitude characterization relative to the contralateral healthy side (absent, normal, or abnormally large). PEMV thresholds and the proportion of abnormally large PEMV across the 6 measurements are recorded.

All recordings are performed by the same examiner within one center using the EcoG module of the Eclipse® system (Interacoustics®).

In each center, the examiner responsible for electrophysiological assessments will have received standardized training by [name] (Associate Professor, University Clermont-Auvergne, and consultant to Interacoustics®).

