**11. STATISTICAL ASPECTS**

**11.1. SAMPLE SIZE CALCULATION**
To evaluate reliability and validity of electrophysiological indicators, the sample size was defined to estimate reliability and validity parameters with sufficient precision.

100 patients with 6 repeated measurements will allow estimation of an intraclass correlation coefficient (ICC) > 0.80 with 95% CI width < 0.10.

Additionally, 100 patients allow the following precision for correlation values:

- 95% CI width < 0.30 for Pearson correlation ≥ 0.50
- 95% CI width < 0.40 for Pearson correlation = 0

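### The section 4.3.1 comparison keeps SP/AP continuous but reduces WBT, and PEMV amplitude where used, to proportions of yes/no readings, which tilts those contrasts towards EcoG

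*Protocol*

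**What the plan says.** Section 4.3.1 makes Pearson coefficients (or standardized regression coefficients) the main validity indicators. It expects a higher correlation with each cardinal symptom for pathological-side SP/AP "than between SCD anatomical size and surface, proportion of 1 kHz absorbance peaks in WBT, or PEMV alteration and symptom severity".

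The measures compared are defined as follows:

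- **SP/AP** (4.2.1.1, 11.2): a ratio computed for each of six recordings and averaged.
- **WBT** (4.2.1.2): the peak and its frequency are determined at each recording. "The proportion of absorbance peaks at 1 kHz (associated with SCD in the literature) across the 6 measurements is also recorded", and this proportion is what 4.3.1 names as the comparator.
- **PEMV** (4.2.1.3): amplitude is classed at each recording as absent, normal or abnormally large relative to the healthy side. "PEMV thresholds and the proportion of abnormally large PEMV across the 6 measurements are recorded". Threshold stays in dB SPL.
- **CT** (4.2.2): largest dimension in mm and surface in mm².

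Section 5.1 gives as the main hypothesis that "the SP/AP ratio measured in electrocochleography will be the parameter most strongly correlated with the cardinal symptoms", relative to the other electrophysiological parameters. Section 3.2 lists the same comparison as a secondary objective.

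**The concern.** A Pearson correlation depends on how a marker is scaled as well as on how well it tracks symptoms. Cutting a continuous reading into yes/no discards part of its relation with symptoms, and more so when nearly all readings fall on one side of the cut. All analysed SCD-side ears are dehiscent, and section 2.1.2.2 says that earlier studies "reported WBT sensitivity of 80–93% for SCD diagnosis", so a high share of positive readings is plausible.

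Only the comparators bear this loss. If SP/AP ranks above WBT, the reader cannot tell whether EcoG is the better marker or WBT was coded more coarsely. That is the comparison on which the section 5.1 hypothesis rests. Nothing in the protocol acknowledges the unequal scales.

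**Working it through.** **1. The plan's own precision figures hold.** Fisher interval tanh(atanh r ± 1.96/√97): the width is 0.297 at r=0.50, which agrees with "95% CI width < 0.30 for Pearson correlation ≥ 0.50", and 0.393 at r=0 (stated: below 0.40). For "100 patients with 6 repeated measurements will allow estimation of an intraclass correlation coefficient (ICC) > 0.80 with 95% CI width < 0.10", the exact F interval gives a width of 0.101 at 0.80 and 0.097 at 0.81, correct within rounding. The sample size is not at fault.

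**2. Inputs.** From the protocol: n=100, six readings, Pearson r, six-reading means. Not in the protocol, and therefore assumed:

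- Normally distributed readings.
- Single-reading ICC of 0.7–0.9.
- The same true validity for both markers.
- Correlation 0.5 between the two markers' true values.
- A share p of positive readings: 80–93% borrows the cited WBT diagnostic sensitivity, 50% is a milder case, and 70% follows the PEMV sensitivity in section 2.1.2.1.

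**3. Attenuation.** For a cut leaving a share p positive, the correlation of the six-reading proportion, divided by that of the six-reading continuous mean, is

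φ(z)/√(p(1−p)) × √[(1+5·ICC)/(1+5·ICC_b)],

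where z is the normal quantile of p and ICC_b is the correlation between two yes/no readings of one ear. The true r cancels. With ICC=0.80:

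| p | φ(z)/√(p(1−p)) | ICC_b | second factor | ratio | ratio for ICC 0.7–0.9 |
|---|---|---|---|---|---|
| 50% | 0.399/0.500 = 0.798 | 0.590 | √(5/3.95) = 1.125 | 0.90 | 0.91–0.88 |
| 70% | 0.348/0.458 = 0.759 | 0.577 | √(5/3.89) = 1.134 | 0.86 | 0.87–0.84 |
| 80% | 0.280/0.400 = 0.700 | 0.556 | √(5/3.78) = 1.150 | 0.80 | 0.82–0.78 |
| 93% | 0.134/0.255 = 0.526 | 0.491 | √(5/3.46) = 1.203 | 0.63 | 0.65–0.60 |

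Simulation with 1,000,000 patients gives the same ratios. If both markers truly correlate 0.50 on six-reading means, the proportion shows 0.39–0.41 at 80% positive and 0.30–0.32 at 93%.

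Averaging six readings does not cure the loss. At ICC 0.80 and 80% positive, 68% of patients score 0/6 or 6/6.

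**4. Effect on the ranking.** 4,000 simulated trials of n=100 per setting, equal validity, ICC 0.7–0.9. The table gives the share of trials in which SP/AP has the higher sample correlation; repeat runs move these figures by a point or two.

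| Positive readings | r=0.50 | r=0.20–0.30 |
|---|---|---|
| 50% | 69–74% | – |
| 80% | 83–88% | 64–73% |
| 93% | 95–97% | 73–85% |
| both continuous | about 50% | about 50% |

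**5. A formal test does not remove it.** With true-value r=0.50 and ICC 0.80, a Williams test for dependent correlations at one-sided 2.5% declares SP/AP higher in 17% of trials at 80% positive and 32% at 90%. With both markers continuous the figure is 2–3%.

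**The case against.** Several points on the other side stand and limit the finding.

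- **Not every comparator is affected.** A reader might infer that the whole comparison favours EcoG by construction. It does not: PEMV threshold and CT size and surface are already continuous. Section 4.3.1 does not say whether PEMV alteration means threshold or amplitude, so the PEMV part applies only where amplitude is used.
- **The positive share is uncertain.** The 80–93% is diagnostic sensitivity from cited work, not the share of single readings with a 1 kHz peak in this cohort. Sections 2.4 and 5.1 deliberately admit patients with few or no symptoms, so the share may be lower. At 50% the loss is only about 10%. To say that WBT loses most of its information fits only the top of the range: squaring the ratios, r² falls by about 60% at 93% positive (1−0.63²) but about 35% at 80% (1−0.80²).
- **WBT may be only weakly related to symptoms**, as section 2.2 expects. The tilt is then smaller, as the r=0.20–0.30 column shows, but it does not vanish.
- **The sign is not wrong.** Section 4 speaks of "verifying positive correlations between symptom impact and electrophysiological or radiological measurements on the pathological side", which might seem to misfit a threshold that falls in SCD. Sections 1 and 3.2 define the indicator as threshold reduction or lowering, so the direction is already built in.
- **No interval for the difference between correlations is given.** A SAP may supply it. Section 4.3.1 states expectations, not a rule that the highest point estimate wins, so the ranking percentages illustrate the tilt and are not error rates of a stated test.
- **WBT recordings yield more than the proportion.** Section 4.2.1.2 determines a peak and its frequency, and section 3.2 speaks of changes in the peak. But 4.3.1 names the proportion, and absorbance at 1 kHz is not clearly required as a number. For PEMV amplitude only a category is required, and a later SAP cannot recover values never entered in the eCRF.

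**Conclusion.** The point holds in a limited form. As written, the SP/AP-versus-WBT contrast, and the PEMV contrast where amplitude is used, sets a continuous six-reading mean against a proportion of yes/no readings. This biases the contrast towards EcoG. The direction was the same in every scenario run; the size depends on the assumed positive share, true r and ICC, and ranges from a loss of about one tenth of the correlation to more than a third.

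The primary objective, SP/AP's own correlation with each symptom, is untouched. What is weakened is any claim that EcoG outperforms WBT or PEMV amplitude. The change should be made before data entry fixes the categories.

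**What to change.** In sections 4.2.1.2 and 4.2.1.3, record absorbance at 1 kHz and PEMV amplitude (side-specific, or as an inter-ear asymmetry ratio) as numbers from the recordings already planned. In section 4.3.1, compare SP/AP with the six-reading means of these continuous values, alongside PEMV threshold lowering and CT size and surface, and state which PEMV measure is meant. Keep the two proportions as descriptive summaries.

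Reporting each difference in correlation with a 95% confidence interval, on the same patients, would be a useful addition; its absence is not an error in the protocol.

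The cost is a few extra eCRF fields and some rewording, with no added test, visit or patient. One downside is that mean absorbance at 1 kHz is not quite the same construct as presence of a 1 kHz peak, which is a reason to keep the proportion descriptively. The other is that a superiority claim for EcoG becomes harder to reach.
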